# The influence of shunting left/right portal vein branch on post-TIPS hepatic encephalopathy: a study protocol for multicenter randomized blinded controlled trial

**DOI:** 10.1186/s13063-023-07326-9

**Published:** 2023-05-06

**Keywords:** Transjugular intrahepatic portosystemic shunt (TIPS), Hepatic encephalopathy (HE), Randomized controlled trial (RCT)

## Abstract

**Introduction:**

Gastroesophageal varices (GOV) bleeding is a common and serious complication of advanced liver cirrhosis with a median survival of less than 2 years. Multiple guidelines have pointed out that transjugular intrahepatic portosystemic shunt (TIPS) is the rescue treatment of acute variceal hemorrhage (AVB) after failure of standard therapy and an effective second-line treatment for preventing patients with high risks from rebleeding of GOV. The safety and stability of TIPS have been greatly improved due to the improvements of related technologies and the emergence of various novel devices, but the incidence of hepatic encephalopathy (HE) after shunting (10–50%) hindered the widespread use of TIPS. The target portal vein branch might affect the incidence of HE after TIPS. The aim of this study is to compare the rate of HE in patients with hepatitis B virus (HBV) related cirrhosis receiving TIPS either the left or right branch of the portal vein with 8mm Viatorr stent for preventing rebleeding from GOV.

**Methods and analysis:**

This study is a multicenter randomized controlled trial comparing the influence of shunting left or right portal vein branch on post-TIPS hepatic encephalopathy for preventing rebleeding from GOV in patients with HBV-related cirrhosis. A total of 130 patients will be recruited over a period of 24 months across 5 centers in China. Eligible patients will be stratified 1:1 to constructing either a left or right portal vein shunt with an 8-mm Viatorr stent. The primary objective was to compare the incidence of post-TIPS hepatic encephalopathy between the two groups. The secondary objectives were to compare the grade and duration of hepatic encephalopathy, the rate of shunt dysfunction, the rate of variceal rebleeding, the HE-free survival, the cumulative patency rate of the stent, and the overall survival at 12 months and 24 months between two groups.

**Ethics and dissemination:**

This study was approved by the ethics committee of Zhongshan Hospital of Fudan University (No. B2018-292R) and was registered at ClinicalTrials.gov (NCT03825848). All participants give written informed consent.

**Trial registration:**

ClinicalTrials.gov NCT03825848. Registered on January 31, 2019

**Trial status:**

The first patient was recruited into our study on June 19, 2019. A total of 55 patients were recruited till May 27, 2021 (27 and 28 patients assigned to shunting the left (L Group) and right (R Group) branches of the portal vein, respectively).

## Introduction

Gastroesophageal varices (GOV) bleeding is a common and serious complication of advanced liver cirrhosis with a median survival of less than 2 years. Despite the continuous improvement of treatments, the mortality rate within 6 weeks after GOV bleeding is as high as 15–25% [1]. Multiple guidelines have pointed out that transjugular intrahepatic portosystemic shunt (TIPS) is the rescue treatment of acute variceal hemorrhage (AVB) after failure of standard therapy and an effective second-line treatment for preventing patients with high risks from rebleeding of GOV [1–4].

The safety and stability of TIPS have been greatly improved due to the improvements of related technologies and the emergence of various novel devices, but the incidence of hepatic encephalopathy (HE) after shunting (10–50%) hindered the widespread use of TIPS [5]. Post-TIPS HE is defined as a brain dysfunction caused by TIPS, it manifests as a wide spectrum of neurological or psychiatric abnormalities ranging from subclinical alterations to coma [6, 7]. None of the administration of aspartic acid/ornithine [8], lactulose [9], or albumin [10] has been proven to effectively prevent the occurrence of HE after TIPS.

On the other hand, the target portal vein branch might affect the incidence of HE after TIPS. The anatomical study suggested that the blood of the portal vein is composed of superior mesenteric venous blood rich in intestinal toxin and splenic venous blood which is relatively. The laminar flow effect may cause the majority of splenic venous blood flow to enter the left branch of the portal vein while the majority of superior mesenteric vein blood flow enters the right branch of the portal vein. An experimental study also found that the blood ammonia concentration in the right branch of the rabbit portal vein was significantly higher than that in the left branch. Some researchers observed that compared with shunting the right branch of the portal vein, the incidence of HE after shunting the left branch was significantly reduced (15.4~28.7% vs 37.5~56.0%) [11–13]. However, the current TIPS-specific stent is applied in none of the above clinical studies, the diameter of the implanted stent is not uniform, the indications for the patients receiving TIPS treatment are different, and the definition of HE after shunting is inconsistent.

To the authors’ knowledge, no controlled, prospective trials have been published to confirm the influence of shunting the left or right branch portal vein branch on post-TIPS HE. For this reason, the Influence of Shunting left/right portal vein branch on post-Transjugular Intrahepatic Portosystemic shunt Hepatic Encephalopathy (INSTIPHE) has been designed as a prospective, randomized, single-blinded, multicenter trial to compare the rate of HE in patients with hepatitis B virus (HBV) related cirrhosis receiving TIPS either the left or right branch of the portal vein with an 8-mm Viatorr stent for preventing rebleeding from GOV. Secondary objectives include comparisons of the grade and duration of hepatic encephalopathy, the rate of shunt dysfunction, the rate of variceal rebleeding, the HE-free survival, the cumulative patency rate of the stent, and the overall survival at 24 months between two groups.

## Methods

### Study design

This study is a randomized, controlled, single-blind, multicenter superiority trial with two parallel groups, comparing the influence of shunting the left or right branch of the portal vein on post-TIPS hepatic encephalopathy in patients with HBV-related cirrhosis. A total of 130 patients will be recruited over a period of 24 months across 5 centers in China. Centers will be chosen based on their potential to recruit a high number of patients and their expertise in TIPS treatment and will receive special training with standard TIPS procedures and HE assessment. Eligible patients will be stratified 1:1 to constructing either a left or right portal vein shunt with an 8-mm Viatorr stent (Fig. 1).

**Fig. 1 Fig1:**
[figure not shown]
Overview of INSTIPHE trial design

This study is conducted in accordance with the Declaration of Helsinki and current good clinical practice guidelines. This study is approved by the ethics committee of Zhongshan Hospital of Fudan University (No. B2018-292R) and was registered at ClinicalTrials.gov (NCT03825848). All other participating centers have obtained the relevant ethics committee approval before patient enrolment.

### Inclusion and exclusion criteria

The inclusion and exclusion criteria for the INSTIPHE trial are summarized in Table 1.

**Table 1 Tab1:** Patient eligibility criteria for INSTIPHE trial

Inclusion criteria	Exclusion criteria
• Written informed consent	• Imaging confirmed portal vein thrombosis
• Aged 18–75 years old	• History of overt hepatic encephalopathy
• Clinically or histologically diagnosed HBV-related cirrhosis by clinical presentations, laboratory tests, images, and liver biopsies)	• History of TIPS or shunt surgery (including splenectomy, surgical disconnection, or shunt)
• History of GOV bleeding confirmed by endoscopy	• Serial ammonia concentration ≥ 100μmol/L
• Rebleeding of GOV after receiving non-selective β-blockers (NSBBs) combined with endoscopic therapy	• Severe liver insufficiency (total bilirubin > 51μmol/L)
• Child-Pugh A or B	• Consolidation of refractory ascites
• Imaging (CT or MRI) suggests that the left/right first branch portal vein of the intrahepatic portal can construct a shunt	• Malignancy or other serious medical illness that may reduce life expectancy
• Adequate hematological function: Neutrophils ≥1500/mm^3^, Platelets ≥50,000/mm^3^, Prothrombin Time (PT) does not exceed the upper limit of normal control for 3 seconds	• Pulmonary artery pressure > 40 mmHg, left ventricular ejection fraction < 50%, congestive heart failure or other severe cardiopulmonary diseases
• Adequate kidney function: Creatinine <150 μmol/L	• Uncontrolled systemic infection or sepsis

### Recruitment and informed consent

We select potential patients strictly according to the indications for TIPS, and introduce our program to patients in detail through posters and videos in our clinics, to attract them to our program. All relevant information regarding the clinical trial is included in informed consent forms in the Chinese language. Furthermore, the principal investigators will provide a detailed explanation of this trial to the eligible patients. Informed consent must be signed by all patients or their relatives if the informed consent cannot be signed by the patients themselves. All patients’ personal data and medical information will be kept confidential. All patients will be permitted to withdraw from this trial at any time.

### Randomization

Eligible patients will be randomized 1:1 into shunting the left (L Group) or right (R Group) branch of the portal vein. The randomization will be stratified by center, Child-Pugh class (Child-Pugh Class A=5–6 points or Child-Pugh Class B=7–9 points), and the serial ammonia level (lower level ≤ 50 µmol/L or higher level >50 µmol/L) before TIPS. The list will be balanced by different-sized blocks and randomly alternated. The treatment assignment of each eligible patients was generated by the web-based system and was contained in opaque envelopes. This randomization procedure was performed by the coordinator, who was isolated from data collection and analysis. The data coordination center of Zhongshan Hospital will prepare the randomization. Patients and clinicians will not be blinded to the shunting branch of the portal vein in TIPS, so the investigators who perform data evaluation and analysis will not participate in the randomization and treatment.

### Protocol treatment

All enrolled patients received TIPS within 72 h of randomization. After transhepatic puncture of a secondary branch of the intrahepatic portal vein under ultrasound guidance, a 5-F Pigtail catheter will be introduced into the splenic vein and superior mesenteric vein (SMV) to evaluate the index varices as well as the feeding vessels and draining veins. The main feeding vessel (e.g., left, short, or posterior gastric vein) will be embolized with coils and N-butyl-2 cyanoacrylate (NBCA). Portal vein pressure and 5ml blood sample for serial ammonia concentration detection will be obtained at the splenic vein, SMV, main portal vein, and primary branch of the intrahepatic portal vein separately. According to the randomization, the tip of the pigtail catheter will be placed at either the left (L Group) or right (R Group) branch of the portal vein (0.5 cm from the portal vein bifurcation) as a marker for conventional TIPS creation. Viatorr-covered stents (W. L. Gore & Associates, USA) with a diameter of 8 mm and a length of 6–10 cm will be employed in our study. Postoperative portal vein pressure will be measured at the main portal vein level. The transhepatic tract will be embolized with coils or NBCA after TIPS.

Low protein diet, intravenous L-ornithine-L-aspartate (20g qd) with branched-chain amino acids, and oral lactulose (10ml tid) for 3 days will be routinely prescribed for the prevention of post-TIPS hepatic encephalopathy after TIPS.

### Trial assessments

The last enrolled patient will be followed up for 24 months after the start of treatment (D0). All other patients will be followed up until the final visit of the last enrolled patient. Patients will therefore be followed up for a maximum of 48 months and a minimum of 12 months following the start of treatment. All patients will be assessed by the schedule summarized in Table 2.

**Table 2 Tab2:** Trial assessment schedule

	Enrollment	Treatment			Post-TIPS follow-up					
Evaluation/examination	≤14 days before randomization	D0	D1	D2	M1	M3	M6	M12	M18	M24
Informed consent	×									
Demographics	×									
Medical History	×									
Enhanced abdominal CT	×			×		×		×		×
Ultrasound Elastography	×			×	×	×	×	×	×	×
Upper gastrointestinal endoscopy	×				×	×	×	×	×	×
Hematology^a^	×	×	×		×	×	×	×	×	×
Biochemistry^b^	×		×		×	×	×	×	×	×
Serial ammonia concentration	×		×		×	×	×	×	×	×
Tumor markers^c^	×		×		×	×	×	×	×	×
HBV-DNA	×		×		×	×	×	×	×	×
Child-Pugh	×		×		×	×	×	×	×	×
MELD^d^	×		×		×	×	×	×	×	×
ECOG^e^	×	×	×	×	×	×	×	×	×	×
HE assessment^f^	×	×	×	×	×	×	×	×	×	×
Adverse events	×	×	×	×	×	×	×	×	×	×
Survival	×	×	×	×	×	×	×	×	×	×

^a^Measurement of red blood cells, hemoglobin, white blood cells, absolute neutrophils and absolute lymphocytes,and platelets

^b^Measurement of total bilirubin, direct and indirect bilirubin, albumin, alanine aminotransferase, aspartate aminotransferase, alkaline phosphatase, glutamine transferase, urea nitrogen, serum creatinine, potassium, sodium, prothrombin time, INR, and D-dimer

^c^Measurement of AFP, CEA, and CA-199

^d^Model for End-stage Liver Disease scores

^e^Eastern Cooperative Oncology Group

^f^Measured by Stroop Test and clinical examination

Additional non-study assessments are permitted at the discretion of the treating investigator. Follow-up will be discontinued if the patient receives liver transplantation, if the patient withdraws consent, or if a physician considers it necessary for the patient to discontinue the trial from a medical perspective.

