### Statistical analysis

All data will be analyzed on the intention-to-treat population and are supplemented by per-protocol set analyses. The intention-to-treat population contains all patients who will undergo randomization (irrespective of whether they successfully receive TIPS), while per-protocol set analyses only include patients who successfully receive TIPS. Continuous variables will be summarized as mean ± standard deviation or the median values (ranges) and will be compared using the independent sample *t* test or one-way analysis of variance. Categorical variables will be expressed as frequencies and compared using the Chi-Square or Fisher’s exact tests. The missing data were performed with multiple imputation by using the MICE procedure. The time-to-event primary and secondary outcomes will be calculated by the Kaplan-Meier method and compared by the log-rank test (Mantel-Haenszel version). Data will be censored when any of the following events occur : liver transplantation, death, end of follow-up time. Estimates of treatment effect (with 95% CIs) were evaluated by using Cox regression models. Two-tailed *p* values <0.05 will be considered statistically significant. All statistical calculations will be performed using SPSS V.25.0 (Chicago, IL, USA).

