### Study limitations

Some aspects of the INTIPHE study design are worth further discussion. First, patients with HBV-related cirrhosis, which is the most common cause of liver cirrhosis in China instead of alcohol abuse in Western countries, are our target population. The difference in the etiology of liver cirrhosis might influence the application of our findings in Western countries. Second, eligible patients in the INTIPHE study will be stratified according to the Child-Pugh score as this is an independent prognostic factor of post-TIPS HE. In addition, patients will be stratified by serial ammonia concentration since it is associated with post-TIPS HE despite not being a valid tool to diagnose HE. Third, the rate of post-TIPS HE has been chosen as the primary endpoint as the episode of HE is a better quantitative indicator than the severity or duration of HE. Fourth, an 8-mm Viatorr covered stent was employed in the INTIPHE trial as recent studies found that compared to the 10mm covered stent, implantation of an 8-mm covered stent significantly reduced the incidence of HE after TIPS without affecting the shunt efficiency. Fifth, while blinding to the physicians is not possible due to the treatment methods, the potential biases caused by the lack of physician blinding will be minimized by appointing an independent group of physicians performing the blind follow-up and diagnosis of post-TIPS HE.

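### Follow-up itself, not only treatment, ends on a physician's medical judgement, so outcome data may be lost for health-related reasons after a one-time procedure

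*Protocol article*

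**What the plan says.** The rule stands under Trial assessments in the protocol article: "Follow-up will be discontinued if the patient receives liver transplantation, if the patient withdraws consent, or if a physician considers it necessary" on medical grounds. The last of the three grounds reads in full: "if a physician considers it necessary for the patient to discontinue the trial from a medical perspective". What ends is follow-up. The sentence gives no criteria and does not say which physician decides.

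Three other sections bear on it:

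- Randomization: "Patients and clinicians will not be blinded to the shunting branch of the portal vein in TIPS". The same sentence keeps the investigators who evaluate and analyse the data out of randomisation and treatment.
- Study limitations: bias from unblinded physicians is to be reduced by "appointing an independent group of physicians performing the blind follow-up and diagnosis of post-TIPS HE".
- Statistical analysis: "The intention-to-treat population contains all patients who will undergo randomization (irrespective of whether they successfully receive TIPS"). The methods are Kaplan-Meier, log-rank and Cox regression. On censoring: "Data will be censored when any of the following events occur : liver transplantation, death, end of follow-up time". On missing values: "The missing data were performed with multiple imputation by using the MICE procedure".

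The primary endpoint (Outcome measures) is overt HE at 24 months. Rebleeding, HE-free survival and overall survival are among the secondary endpoints.

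**The concern.** A rule of this kind is usually written for a drug that can be stopped for safety. Here the randomised intervention is one shunt placement. Protocol treatment adds three days of routine HE prophylaxis for all patients, and no randomised treatment continues after that. A physician who invokes the clause therefore withdraws nothing that was randomised. What ends is the recording of HE, rebleeding and survival.

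The stated ground is medical, so the decision depends on the patient's health. In patients with cirrhosis and a new shunt, health may well be related to the risk of HE or death. If so, the patients whose data stop early differ in prognosis from those still observed. If the clause is also used differently in the two arms, the primary comparison is distorted in a way that depends on who was stopped. No later analysis can recover events that were never recorded.

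**Working it through.** **Step 1. How a stopped patient enters the analysis.** Discontinuation by a physician is not named in the censoring list, which leaves two readings.

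- It counts as the end of follow-up. The patient is censored at that date, and Kaplan-Meier, log-rank and Cox assume that the censoring carries no information about later HE.
- The remaining outcome counts as missing and is imputed. Multiple imputation in its standard form assumes that the data are missing at random given what was recorded.

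A stop based on medical judgement puts both assumptions in doubt. Imputation helps to the extent that the reason for stopping is captured in recorded variables. It does not help where the decision rested on unrecorded health status.

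**Step 2. How large the effect could be.** The article gives no frequency of stopping and no outcome rate in stopped patients, so both are assumed.

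Inputs from Sample size calculation: 24-month HE rates of 16.9% (left) and 33.1% (right), a difference of 33.1 − 16.9 = 16.2 points. With 130 patients at 1:1 there are 130/2 = 65 per arm.

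Assumed: *f*, the fraction of an arm stopped before any HE, and *h*, the HE risk those patients would have had by month 24, taken as 0.5 to 0.9. If only patients still followed are counted,

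observed rate = (p − f × h) / (1 − f).

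*Equal stopping, f = 0.10 in both arms (6.5 of 65 patients):*

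| h | Left | Right | Difference |
|---|---|---|---|
| 0.5 | (0.169 − 0.050)/0.90 = 13.2% | (0.331 − 0.050)/0.90 = 31.2% | 18.0 points |
| 0.9 | (0.169 − 0.090)/0.90 = 8.8% | (0.331 − 0.090)/0.90 = 26.8% | 18.0 points |

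Both rates fall, but the difference widens. With the same f and h in both arms, f × h cancels and the difference is 0.162/0.90 = 0.180 whatever h is.

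*Unequal stopping, f = 0.03 left and 0.12 right (about 2 and 8 of 65 patients):*

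| h | Left | Right | Difference |
|---|---|---|---|
| 0.5 | (0.169 − 0.015)/0.97 = 15.9% | (0.331 − 0.060)/0.88 = 30.8% | 14.9 points |
| 0.9 | (0.169 − 0.027)/0.97 = 14.6% | (0.331 − 0.108)/0.88 = 25.3% | 10.7 points |

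**Step 3. Sensitivity to the form of the assumption.** Suppose instead that stopped patients carry twice the HE risk of their own arm, so that h = 2p.

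- 10% stopped in each arm: 15.0% and 29.4%, a difference of 14.4 points.
- 5% left and 15% right: 0.169 × 0.90/0.95 = 16.0% and 0.331 × 0.70/0.85 = 27.3%, a difference of 11.2 points (before rounding).
- 15% left and 5% right: 0.169 × 0.70/0.85 = 13.9% and 0.331 × 0.90/0.95 = 31.4%, a difference of 17.4 points (before rounding).
- If stopped patients have the same risk as the rest of their arm, the difference stays at 16.2 points.

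Even the sign of the bias under equal stopping depends on the assumption: 18.0 points with a common absolute risk, 14.4 with a common risk ratio.

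**The case against.** **The decision-maker may be blinded.** A reader might infer that physicians who know the arm take the decision. The article does not say so. It says only that a physician decides, and Study limitations places follow-up and HE diagnosis with an independent blinded group. That stands: use by unblinded clinicians is possible, not documented. It does not dispose of the point, because the blinded group is not given this decision, and a blinded stop on medical grounds could still be related to outcome.

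**Loss in the sickest patients is an inference.** It follows plausibly from the medical ground, but no section gives criteria, frequency or direction. This stands.

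**It does not contradict intention-to-treat.** A reader might say that the rule conflicts with an analysis of all randomised patients. It does not. That population is defined by randomisation, and stopped patients remain in it with their data up to the stop. A patient stopped after a first overt HE episode loses nothing on HE incidence.

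**The arithmetic is not the planned analysis.** Correct. The formula drops stopped patients completely, as if all stops came before any event. Kaplan-Meier and Cox keep event-free time up to the stop, and imputation is planned as well. A risk of 50 to 90% is also about 3 to 5 times the left arm's 16.9%. The figures illustrate and do not predict.

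**The article is condensed.** Who decides and how reasons are logged may stand in a full protocol, and their absence here is not held against the plan. The rule that follow-up ends is stated, however, and an analysis plan cannot restore outcomes that this rule stops collecting.

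**Conclusion.** The clause is a badly fixed rule and should be changed. As written, it ends outcome collection for a health-related reason in a trial where no randomised treatment remains to be stopped. Neither non-informative censoring nor standard multiple imputation can be relied on to repair such a loss. The intention-to-treat comparison is weakened, not contradicted.

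The size cannot be known from the article. Under the assumed stopping fractions and risks, a true difference of 16.2 points would be observed as 18.0 points with equal 10% stopping, and as 14.9 to 10.7 points with 3% left and 12% right. A reader might take the clause as a cause of dilution, but that is not supported. In the main illustration the difference shrinks only under the assumed imbalance between arms, for which the article gives no evidence, and the bias can go either way. The 10% dropout allowance in the sample size covers the number of patients lost, not this bias.

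**What to change.** Remove the physician-decision clause as a reason to end outcome collection. Scheduled visits may still stop. State that:

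- HE episodes, rebleeding and vital status are collected to month 24 for every randomised patient unless the patient withdraws consent to data collection;
- where visits are not feasible, this is done by telephone or record review;
- the date, reason and decision-maker of each stop are recorded and tabulated by arm.

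This concerns data collection only and changes no treatment. How the analysis handles transplantation is a separate question that it leaves untouched.

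The cost is a short protocol amendment, which in a running five-centre trial has to go through the ethics committees concerned, and a few extra telephone or record contacts. Patients whose follow-up has already been ended under the clause could be identified and their reasons tabulated at the same time.
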